### Study population

Adult patients with an indication for elective left lateral sectionectomy and left hemihepatectomy because of left intrahepatic bile duct stones with irreversible disease, such as biliary strictures, severe parenchymal fibrosis, or atrophy.

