### Randomization

Patient recruitment and the collection of written informed consent will be performed at the outpatient clinic. Patients will be randomized to the different groups using the block randomization method. Each block contains two groups: the OLH group and the LLH group. The block size will be hidden from the trial executors and clinicians. Possible balanced combinations of these groups within the block will be numbered consecutively. Then, blocks will be randomly chosen using the ‘randomize’ library of SPSS 22.0 (SPSS, Chicago, USA), and a series of randomly assigned OLHs and LLHs will be generated based on the random sequence of blocks. Allocation will be concealed using sequentially numbered, sealed opaque envelopes prepared by a member of our Clinical Trial Center. Patients will be randomly allocated to either OLH or LLH before surgery. The trial executors will receive randomly generated treatment allocations within sealed opaque envelopes. Afterwards, medical staff will personally inform the expert surgeon as to which treatment group the patient has been randomized. To avoid any potential prediction of group allocation, information on the block length will be kept away from the study site.

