### Secondary endpoints

The secondary outcomes are biliary leak [19], haemorrhage [20], posthepatectomy liver failure [21], wound infection, intra-abdominal fluid collection or abscess, relaparotomy, mortality, long-term abdominal wall hernias, hospital costs, residual stone rate and recurrence of calculus [22]. Existent ISGLS definitions will be used to ensure the comparability and generalizability of the results. Postoperative complications will be graded based on severity according to the Clavien–Dindo definition [27] (Tables 1 and 2).

**Table 1 Tab1:** Definition of the secondary endpoints

Secondary endpoint	Definition and assessment of outcomes
Operative time	Time from beginning to end of operation
Mortality	Death due to any cause until 90 days after the operation and the reason
Morbidity	Postoperative complications will be recorded until 90 days after operation. The severity of complications will be graded according to the Clavien–Dindo classification [27]
Blood loss	Total blood loss during the operation
Intraoperative blood transfusion	Massive haemorrhage with hemoglobin level < 7 g/dl or Hct < 22
Postoperative hospital stay	Time from the day of operation until discharge(days)
Post-hepatectomy haemorrhage	Evidence of blood loss from drains and/or nasogastric tube, based on ultrasonography, as defined by ISGPS (grade A, B, or C) [20]
Biliary leak	Bilirubin concentration in the drain fluid at least three times the serum bilirubin concentration as defined as ISGLS (grade A, B or C) [19]
Post-hepatectomy liver failure	The impaired ability of the liver to maintain its synthetic, excretory, and detoxifying functions, which are characterized by an increased international normalized ratio and concomitant hyperbilirubinemia (according to the normal limits of the local laboratory) on or after postoperative day 5 as defined as ISGLS (grade A, B, or C) [21]
Intraabdominal fluid collection	Collection of fluid measuring ≥ 3 cm associated with clinical or laboratory abnormalities
Pneumonia	Presence of a new infiltrate on chest X-ray, as well as following: body temperature > 38℃, abnormal elevation of WBC, or positive sputum, and requiring antibiotic treatment
Wound infection	Surgical site infection associated with laparotomy that develops during the initial hospital stay
Abdominal rupture	Dehiscence of abnormal closure with need for resuture of the laparotomy during the initial hospital stay

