Total hospitalization expenses	Hospital costs from admission to discharge ($)
Recurrence of calculus	Calculi in the intrahepatic duct within 3 months after hepatectomy are defined as residual stones [22]

**Table 2 Tab2:** Severity grade according to the Clavien–Dindo definition [27]

Grade	Definition
I	Any deviation from the normal postoperative course without the need for pharmacological treatment or surgical, endoscopic, and radiological intervention
II	Requiring pharmacological treatment with drugs other than those allowed for grade I complications
III	Requiring surgical, endoscopic, or radiological intervention
IIIa	Intervention not under general anaesthesia
IIIb	Intervention under general anaesthesia
IV	Lifer-threatening complication. Requiring intensive care unit management
IVa	Single-organ dysfunction
IVb	Multiorgan dysfunction
V	Death of patient

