#### Statistical analysis

The two-sided null hypothesis for the primary endpoint states that both study interventions will lead to a similar time to the LOS; the alternative hypothesis is that one intervention will perform better than the other. The null hypothesis will be tested by analysing the covariance while adjusting for age and the type of liver resection. A binary logistic regression will be applied to compare the time to functional recovery between groups after adjusting for other factors. Background characteristics and surgical outcome measures will be compared using chi-squared or Fisher’s exact tests for categorical data and two-tailed* t* tests or nonparametric Mann–Whitney *U* tests for continuous variables. Categorical data will be presented as the frequencies and group percentages, and continuous variables will be expressed as the means and standard deviations. The homogeneity of the two groups will be described by comparison of the demographic data and baseline values. All analyses will be performed on an ITT basis [17]. For the ITT analyses, the data will be processed for all trial patients in their randomized groups. A *P* value < 0.05 will be considered statistically significant. All statistical calculations will be performed using SPSS 22.0 (SPSS version 25, IBM statistics, Chicago, IL, USA).

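### Length of stay is adjusted for age and resection type, but the other surgical outcomes get unadjusted tests: valid, yet some precision is given up and a realised imbalance in resection type is left uncorrected

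*Protocol article*

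**What the plan says.** All places are in the protocol article.

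- **Primary outcome (Statistical analysis).** "The null hypothesis will be tested by analysing the covariance while adjusting for age and the type of liver resection".
- **Functional recovery (same section).** This outcome also has an adjusted model: "A binary logistic regression will be applied to compare the time to functional recovery between groups after adjusting for other factors".
- **Other outcomes (same section).** "Background characteristics and surgical outcome measures will be compared using chi-squared or" Fisher's exact tests for categorical data, and t or Mann–Whitney U tests for continuous data. Baseline characteristics and outcomes share this one sentence, and it names no covariates.
- **Outcomes concerned (Secondary endpoints, Table 1).** Operative time ("Time from beginning to end of operation"), blood loss ("Total blood loss during the operation") and total hospitalization expenses ("Hospital costs from admission to discharge"). The analysis section names none of the three and gives no other method for them.
- **Population (Study population).** "Adult patients with an indication for elective left lateral sectionectomy and left hemihepatectomy". The expected mix of the two operations is not stated.
- **Allocation (Randomization).** "Patients will be randomized to the different groups using the block randomization method". No stratification by resection type is described.

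**The concern.** The plan's own primary model treats age and resection type as prognostic. It is plausible, though the document does not show it, that time in theatre, blood loss and cost also depend on how much liver is removed. If so, an unadjusted comparison leaves the variation between the two operations in the error term, and its confidence interval is wider than it need be.

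Without stratification, one arm may also receive more hemihepatectomies by chance. The LOS analysis would correct for that; the comparisons of operative time, blood loss and cost would not.

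At stake are the precision and readability of secondary results. The primary conclusion is not affected. Since the Discussion calls the sample small and sees the trial as informing larger ones, well-estimated secondary differences have some value.

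**Working it through.** **1. The plan's own figure.** Sample size calculation gives 86 per group for a 1-day difference (5 against 6 days), two-sided α = 0.05 and 90% power. No SD is stated. Assuming SD = 2 days:

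- Normal approximation: n = 2 × (1.960 + 1.282)² × 2² / 1² = 84.1, so 85.
- Two-sample t test: 85.03, so 86, as stated.

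The total is 2 × 86 + 18 = 190. These figures rest on LOS alone, so nothing below changes them.

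**2. Precision.** Let R² be the share of an outcome's variance explained by age and resection type. The ratio of adjusted to unadjusted standard error (SE) is √(1 − R²), and the equivalent gain in patients is 1/(1 − R²). The document gives no R², so a range is shown. The last column takes a contrast with 80% power unadjusted: power = Φ[(1.960 + 0.842)/√(1 − R²) − 1.960].

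| R² (assumed) | SE ratio | Fall in SE | Equivalent n | 80% power becomes |
|---|---|---|---|---|
| 0.05 | 0.975 | 2.5% | × 1.05 | 82% |
| 0.10 | 0.949 | 5% | × 1.11 | 84% |
| 0.20 | 0.894 | 11% | × 1.25 | 88% |
| 0.30 | 0.837 | 16% | × 1.43 | 92% |
| 0.40 | 0.775 | 23% | × 1.67 | 95% |

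To give R² a meaning: for resection type alone, with a share p of one type and a difference of D within-type SDs, R² = p(1 − p)D² / [1 + p(1 − p)D²]. With p = 0.5, D = 0.5, 1.0 and 1.5 give 0.0625/1.0625 = 0.06, 0.25/1.25 = 0.20 and 0.5625/1.5625 = 0.36.

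**3. Size of a chance imbalance.** The SD of the between-arm difference in resection mix is √[2p(1 − p)/n], treating allocation as unstratified.

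- 86 per arm, 50:50 mix (assumed): √(0.5/86) = 7.6 points; 95% range about ±15 points; chance of a difference above 10 points, 19%.
- 86 per arm, 30:70 mix: 7.0 points; about ±14 points; 15%.
- 95 per arm, 50:50 mix: 7.3 points; about ±14 points; 17%.

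**4. Effect of an imbalance on the unadjusted contrast.** At R² = 0.20 and p = 0.5 the type effect is √0.20/0.5 = 0.894 outcome SDs. A 10-point imbalance shifts the contrast by 0.10 × 0.894 = 0.09 SD. The unadjusted SE is √(2/86) = 0.15 SD, so the shift is about 0.6 SE.

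**5. Validity.** In 20,000 simulated trials with 86 per arm, R² = 0.20, a 50:50 mix and no treatment effect, the unadjusted t test rejected in 4.9%. Averaged over randomizations, it holds its level.

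Given a particular imbalance, the rate differs. At R² = 0.20 the critical value is 1.96 × 0.1525 = 0.299 SD, and the SE conditional on the mix is 0.1525 × 0.894 = 0.136 SD.

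- Balanced mix: 2 × [1 − Φ(0.299/0.136)] = 2.8%.
- 10-point imbalance (shift 0.089): 6.5%.
- 15-point imbalance (shift 0.134): 11.4%.

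At D = 0.5 (R² = 0.06) the last two rates are 5.5% and 6.9%. The adjusted analysis stays near 5% throughout.

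**The case against.** The case against is substantial.

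- **The planned tests are standard.** Between randomized arms they are unbiased over randomization, and chance imbalance is already reflected in their SE and P value. This stands in full. A reader might infer that the unadjusted comparisons are biased or invalid; the 4.9% simulated error shows otherwise. The conditional rates above show only what adjustment would add once a particular imbalance has occurred.
- **The covariate sets need not match.** Using covariates for the primary outcome and none for unpowered secondary outcomes is permissible. This also stands: it is no contradiction in the plan.
- **The gain cannot be derived from the document.** R² and the resection mix are assumptions, and the range runs from negligible to material. This stands, and it sets the low priority.
- **The scope is partly inferred.** Operative time, blood loss and especially costs are assigned to the unadjusted tests by reading the sentence together with Table 1. Not every other outcome is unadjusted either, since functional recovery has an adjusted model. Both limits are accepted. The absence of stratification is likewise read from silence in a condensed article.
- **The detail may belong in the statistical analysis plan.** This does not carry. The article is not silent: it names the tests for these outcomes, and a better choice is available at little cost.

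**Conclusion.** The point holds as an efficiency improvement of optional priority. The plan fixes unadjusted tests for surgical outcome measures although its own primary model treats age and resection type as prognostic. Those tests are valid; they forgo precision and leave a realised imbalance in resection type uncorrected.

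The size rests on an assumed R². It is negligible near 0.05 (SE down 2.5%) and material from about 0.20 (SE down 11%), reaching 23% at 0.40. The imbalance figures further assume a 50:50 or 30:70 mix and no stratification.

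A reader might also infer that primary and secondary results could point in opposite directions for this reason alone. The document does not support that. A 10-point imbalance at R² = 0.20 moves the contrast by about 0.6 SE, which would reverse its sign only if the estimated difference were otherwise close to zero.

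**What to change.** In Statistical analysis, state that the continuous secondary outcomes (operative time, blood loss and hospital costs) will be analysed with the same covariance model as LOS: arm, age and resection type. Define resection type as the operation planned before randomization. The type actually performed is known only after allocation and could be influenced by it, and the present wording does not say which is meant.

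Use a log scale for blood loss if it is skewed. Keep costs on the mean scale with robust standard errors. Report adjusted differences with 95% confidence intervals.

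**Cost.** One or two sentences, with no change to the 86 per group or the total of 190. The planned operation should be known from the elective indication, but it must be recorded before randomization as its own variable, and residuals must be checked. The categorical outcomes need no change for this point.

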### Definitions

Functional recovery is reached when all of the following criteria are met: adequate pain control with only oral analgesia, restoration of mobility to a level of independence, ability to maintain sufficient caloric intake (a minimum of 50% of the required daily intake), no need for intravenous fluid administration, and no signs of active infection (fever or other clinical symptoms) [15]. Complications will be classified using the Clavien–Dindo score [27]. Major complications will be defined as a Clavien–Dindo grade III or higher.

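### If complication grades themselves are compared, the only test named for categorical data ignores their order; name an ordinal method for that comparison (minor, secondary endpoint)

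*Protocol article*

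**What the plan says.** Under Secondary endpoints, the protocol article states that "Postoperative complications will be graded based on severity according to the Clavien–Dindo definition". The morbidity row of Table 1 repeats this ("The severity of complications will be graded according to the Clavien–Dindo classification") and sets the window: "Postoperative complications will be recorded until 90 days after operation". Table 2 lists the grades I, II, IIIa, IIIb, IVa, IVb and V. Biliary leak is recorded "as defined as ISGLS (grade A, B or C"), and haemorrhage and liver failure also carry A to C grades.

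The Definitions section adds one binary cut: "Major complications will be defined as a Clavien–Dindo grade III or higher".

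Under Statistical analysis, "surgical outcome measures will be compared using chi-squared or Fisher’s exact tests for categorical data". The same sentence offers t tests or the Mann–Whitney test, but as "tests for continuous variables". On presentation, "Categorical data will be presented as the frequencies and group percentages". The article names no trend, rank or ordinal method for graded outcomes. It also does not say that a full table of grades will be tested.

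**The concern.** A chi-squared or Fisher test on a table of arm by grade gives the same P value whatever order the grades are in. Swapping grade I with grade V changes nothing. The clinical question has a direction (are complications less severe after laparoscopic surgery?), yet such a test spreads its sensitivity over every possible pattern. With *none* plus seven Clavien–Dindo grades, that is up to 7 degrees of freedom, and many cells are close to empty at this sample size.

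The trial aims to compare safety as well as effectiveness, and morbidity is a named secondary outcome. If the grades were compared in this way, a non-significant result would carry little information but could be read as similar safety.

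This is more than a detail left to an analysis plan. The article assigns one kind of test to all categorical outcome measures, and a later plan would have to depart from that text to use the order.

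**Working it through.** **No figure in the plan to reproduce.** The protocol gives no rate, effect size or power for morbidity. Its 86 per group was calculated for length of stay and is used here only as the number of patients per arm.

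**Inputs**
- From the protocol: 86 per arm, two-sided 5% level, Clavien–Dindo grades as in Table 2 with *none* added (8 ordered categories).
- Assumed: any complication in 25, 35 or 45% of the open arm. Complications split over I/II/IIIa/IIIb/IVa/IVb/V as 30/40/12/8/5/3/2%. Common odds ratio 0.5 for a worse grade with laparoscopy.

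**Rates implied in the laparoscopic arm** (odds × 0.5, then odds/(1 + odds))
- 25%: 0.333 × 0.5 = 0.167, giving 14.3%
- 35%: 0.538 × 0.5 = 0.269, giving 21.2%
- 45%: 0.818 × 0.5 = 0.409, giving 29.0%
- Grade III or higher is 30% of complications in the open arm: 7.5, 10.5 and 13.5%. The same shift gives 3.9, 5.5 and 7.2%.

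**Tests compared by simulation**
- Grade table: X² = Σ(O − E)²/E on (non-empty grades − 1) degrees of freedom.
- Mann–Whitney on grade, with tie-corrected variance (n²/12)·[(N + 1) − Σ(t³ − t)/(N(N − 1))], where n = 86, N = 172 and t is the number of patients in each grade.
- Chi-squared on any versus none.
- Fisher on grade III or higher.

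**Result 1: common shift, odds ratio 0.5**

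| Any complication, open arm | 25% | 35% | 45% |
|---|---|---|---|
| Chi-squared on grade table | 16% | 22% | 30% |
| Mann–Whitney on grade | 43% | 53% | 61% |
| Chi-squared, any versus none | 42% | 52% | 60% |
| Fisher, grade III or higher | 9% | 15% | 21% |

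The grade-table test is 27, 31 and 31 points below the rank test. With no true difference it rejects in only 2.6 to 3.4% of trials, so part of the loss comes from sparse cells. Any versus none is within 1 point of the rank test. Fisher on grade III or higher is weak because events are few and the scale is cut there, not because it ignores order.

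Hand check of one cell (25% versus 14.3%): difference 0.107, standard error under the null √(2 × 0.196 × 0.804/86) = 0.0606, under the alternative √((0.1875 + 0.1224)/86) = 0.0600. Then (0.107 − 1.96 × 0.0606)/0.0600 ≈ −0.19, a power of about 42%, as simulated.

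**Result 2: other assumed distributions, same odds ratio.** With six categories and any-complication rates of 20/30/40/55%, the grade table has 18/26/33/40% power, Mann–Whitney 36/49/57/66%, and any versus none 35/49/55/63%. For an A to C scale with 15% events in the open arm, the four-category table has 16%, Mann–Whitney 28% and yes/no chi-squared 28%.

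**Result 3: severity shifts, overall rate equal.** The any-complication rate is the same in both arms, and the share of complications at grade III or higher falls from 30% to 5% with laparoscopy (assumed).

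| Any complication, both arms | 25% | 35% | 45% |
|---|---|---|---|
| Mann–Whitney on grade | 6% | 7% | 10% |
| Chi-squared on grade table | 14% | 26% | 43% |
| Fisher, grade III or higher | 34% | 59% | 73% |

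Here the rank test is the weakest. When most patients have no complication, it is largely a test of any versus none.

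**The case against.** The strongest reply is that the article never commits to testing a table of grades. It lists most complications as separate events, defines major complications as a yes/no outcome and reports categorical data as counts and percentages. Chi-squared or Fisher suits all of these, and recording a grade is not a plan to test it. This stands, and it is why the point is conditional. A reader might infer that the stated tests lose much of the power of the morbidity comparison as a whole. The documents do not support that: any versus none falls within the stated rule and nearly matches the rank test.

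A second reply is that a common shift is the setting that favours a rank test. This also stands. Result 3 shows that an ordinal test is not always stronger, so it would be wrong to make grade III or higher merely descriptive once an ordinal test is added.

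A third reply is that a statistical analysis plan, listed in the article among the documents to be shared, may settle the method. It may. But the article is not silent: it gives a rule for categorical outcomes and reserves the rank test for continuous ones. The part of this reply that stands is the low weight, since morbidity is secondary and the sample size rests on length of stay alone.

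**Conclusion.** The point holds in a limited form and is minor. The protocol collects severity on ordered scales, and the only test it states for categorical outcomes cannot use the order. If the grades are compared under that rule, about 27 to 31 points of power are lost against a rank test at an odds ratio of 0.5 (16 to 30% against 43 to 61%). The second set of assumed distributions gives a loss of 18 to 26 points.

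These sizes depend on assumed complication rates, grade splits and a common shift across grades, none of which the protocol supplies. No comparable loss applies to any complication versus none. The low power at grade III or higher is a matter of few events, not of the test chosen. The protocol nowhere calls morbidity its main safety comparison, so the point does not threaten the trial's principal conclusion.

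**What to change.** Add a sentence to Statistical analysis: where severity is compared, each patient's worst Clavien–Dindo grade to 90 days, with *none* as the lowest category, is analysed by a tie-corrected Mann–Whitney test or by proportional-odds logistic regression with a common odds ratio and 95% confidence interval. Treat the A to C grades of leak, haemorrhage and liver failure in the same way. If the model is adjusted, use the covariates of the primary model: age and type of liver resection.

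Keep chi-squared or Fisher for binary and nominal outcomes, including any complication and grade III or higher. Both should remain tested comparisons, and the full grade table should still be shown.

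The cost is a sentence or two, with no new data or patients, and the methods are available in SPSS. Two downsides should be acknowledged. The common odds ratio assumes a similar shift across grades, and the rank test mostly reflects any versus none when most patients have no complication. The wording should be fixed before outcomes are seen by arm.

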### Frequency and plans for auditing trial conduct

The principal investigator will submit an interim report every 12 months, and auditing will be conducted annually by designated members of the Medical Research Collaborating Center (MRCC) from the Second Hospital of Anhui Medical University. The auditing process will be independent of the investigators and the sponsor.

